## Abstract

**Introduction:**

The latest chronic obstructive pulmonary disease (COPD) epidemiology survey in China estimated that there were 99 million potential COPD patients in the country, the majority of whom are undiagnosed. Screening for COPD in primary care settings is of vital importance for China, but it is not known which strategy would be the most suitable for adoption in primary care. Studies have been conducted to test the accuracy of questionnaires, expiratory peak flow meters and microspirometers to screen for COPD, but no study has directly evaluated and compared the effectiveness and cost-effectiveness of these methods in the Chinese setting.

**Methods and analysis:**

We present the protocol for a multicentre cross-sectional study, to be conducted in eight community hospitals from four cities among Chinese adults aged 40 years or older to investigate the effectiveness and cost-effectiveness of different case-finding methods for COPD, and determine the test performance of individual and combinations of screening tests and strategies in comparison with quality diagnostic spirometry. Index tests are screening questionnaires (COPD Diagnostic Questionnaire (CDQ), COPD Assessment in Primary Care To Identify Undiagnosed Respiratory Disease and Exacerbation Risk Questionnaire (CAPTURE), symptom-based questionnaire, COPD Screening Questionnaire (COPD-SQ)), microspirometer and peak flow. Each participant will complete all of these tests in one assessment. The primary analysis will compare the performance of a screening questionnaire with a handheld device. Secondary analyses will include the comparative performance of each index test, as well as a comparison of strategies where we use a screening questionnaire and a handheld device. Approximately 2000 participants will be recruited over 9 to 12 months.

**Ethics and dissemination:**

The study has been approved by Peking University Hospital and University of Birmingham. All study participants will provide written informed consent. Study results will be published in appropriate journal and presented at national and international conferences, as well as relevant social media and various community/stakeholder engagement activities.

**Trial registration number:**

ISRCTN13357135.

Strengths and limitations of this studyThis is the first study to compare the effectiveness and cost-effectiveness of selected screening tests (questionnaires, peak flow meter and microspirometer) and strategies to screen for chronic obstructive pulmonary disease (COPD) in China.Recruiting participants from both urban and rural community hospitals will maximise the generalisability to primary care patients.Including four different screening questionnaires enables comparison of their test performance within a Chinese COPD population.Using blinded researchers to administer quality diagnostic spirometry minimises the risk of reviewer bias.The study will be conducted in four cities across China, which are geographically disparate but may not be representative of China as a whole.

## Introduction

Chronic obstructive pulmonary disease (COPD) is a common, preventable and treatable chronic condition characterised by persistent respiratory symptoms and airflow limitation.^1^ Despite COPD being the third leading cause of death in the world,^2^ COPD is underdiagnosed throughout the world due to multiple reason, including low awareness of the disease and its consequences among the public and primary care health professionals, and the low use of spirometry.^3^ While studies report the prevalence of undiagnosed COPD as being approximately 70% in Spain^3^ and Poland^4^ among those with the condition, a recent study in China reported that 96% of those with spirometry-confirmed COPD did not have a diagnosis.^5^ Data from the US National Health and Nutrition Examination Survey revealed those with undiagnosed COPD were characterised by fewer symptoms,^6^ this is reflected in China where 68% of undiagnosed people were asymptomatic.^7^ What’s more, about 30% of COPD patients were asymptomatic, those people were more likely to be underdiagnosed.^4 8^

The Global Initiative for Chronic Obstructive Lung Disease (GOLD) defines individuals as being at high risk of COPD if they have chronic respiratory symptoms, exposure to risk factors or medical/family history of respiratory disease.^1^ According to the above definition, about 90% of people aged ≥40 years in China were at high risk of COPD in 2014.^9^ The prevalence of diagnosed COPD in China was 13.7% in 2015.^5^ Considering the substantial proportion of the Chinese population that is at risk of undiagnosed disease, screening for COPD in China is essential. Recently, China called for national policies and programmes for the prevention and early detection of COPD.^5 10^ In line with this, government agencies have recommended the incorporation of pulmonary function tests into routine health examinations in China’s thirteenth five-year plan for healthcare.^11^

While guidelines recommend that COPD is diagnosed based on spirometry and symptomology,^1^ spirometry is not always available in primary care settings in China.^12 13^ Among a large population of COPD patients in China, less than 12% had ever been tested using spirometry.^5 10^ As a result, there is a need for simple and affordable COPD screening tools in primary care settings.

While COPD screening programmes are not currently recommended by the USA^14^ or UK^15^ due to insufficient evidence of health benefits, the national policy do recommend screening for undiagnosed COPD in China.^11^ Despite the support for screening in China, there is no recommendation on the best strategy or approach to use. Multiple screening questionnaires have been developed to identify patients at risk of COPD, either in primary or secondary care settings.^16–20^ Questionnaire items include the presence of respiratory symptoms (eg, wheeze, dyspnoea and cough) while some tools also explore exposures, smoking history and age. The questionnaires are all designed to be self-completed, but vary regarding the populations in which they were developed/validated, for example, general population or targeted groups such as symptomatic patients or current smokers. Microspirometers are small handheld devices that measure lung function, which are low cost, quick to use and require minimal coaching for patients. Peak flow monitors are simple, low-cost devices that measure how much air patients can expel during a forced expiration (peak expiratory flow, (PEF)), and evidence indicates that these devices may also be suitable as a possible screening tool for COPD.^18 21 22^

Screening tests can be used individually or in combination as screening ‘strategies’. Systematic reviews and more recent primary studies typically assess the use of a single test, concluding that many of the available tests may be appropriate for use in COPD screening.^23–25^ However, studies in community settings in China are limited and it is not known which screening test or strategy would be most appropriate to use. As a middle-income country with a large potential COPD population, it is important to explore the most effective and cost-effective screening strategy. Accurately detecting individuals who merit referral for quality diagnostic spirometry could minimise the number of ineligible referrals, thus protecting health system resources and ensuring appropriate and timely treatment for those subsequently diagnosed.

## Aims and objectives

### Aim

The aim of the study is to identify the most effective and cost-effective screening strategy for identifying undiagnosed COPD among those aged 40 years or older in China.

### Objectives

To determine the comparative test performance of all screening tests and strategies in diagnosing COPD (confirmed by quality diagnostic spirometry).To evaluate the cost-effectiveness of each screening strategy.

## Methods and analysis

Study recruitment commenced in February 2019 and ended in December 2019.

### Design

Multicentre cross-sectional test accuracy study. The study is registered at http://www.isrctn.com.

The Standards for Reporting of Diagnostic Accuracy Studies guideline^26^ was used for reporting studies of diagnostic test accuracy to inform the content of the protocol and we will use this to report the study.

### Study setting

The study will be implemented in four cities in China: Beijing (North), Chengdu (Southwest), Guangzhou (South) and Shenyang (Northeast). Cities were purposively selected to represent urban/rural settings and differing geographic areas of the country, where exposures, lifestyles and the prevalence of COPD may differ. The national study about COPD prevalence in 2007 in China was taken as a selection reference. Each selected city had the highest prevalence of COPD in each geographic area; prevalence is shown on the map.^27^ Participants will be recruited from eight community health service centres (CHSC); one rural and one urban in each city. The study sites are shown on the map (figure 1).

**Figure 1 F1:**
[figure not shown]
The map of Breathe Well China research sites. CHSC, community health service centre.

### Study population

#### Inclusion criteria

Aged ≥40 years.Residing in the catchment areas of the participating CHSCs in the four cities.

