#### Exclusion criteria

Unable to perform spirometry (eg, dementia or lack of teeth-cannot make a good seal).Contraindicated for spirometry (chest infection in the last 3 weeks, coughing up blood in the last month, severe angina, uncontrolled high blood pressure, pneumothorax or history in the last 3 months of tuberculosis, heart attack, detached retina or surgery on chest/abdomen/brain/ears/eyes).Currently pregnant/breastfeeding.Previous adverse reaction to salbutamol.

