### Recruitment

Participants will be recruited to the study via two main routes, advertisement or doctor referral. Participating CHSCs and their satellite offices will advertise the study by displaying posters and sending messages to their secure/closed/other resident WeChat social media groups, inviting residents to contact the research team if they are interested in taking part. Potentially eligible patients visiting the participating CHSCs will be given a study information sheet by the healthcare professionals and invited to attend a study assessment with researchers. Study participants will also be encouraged to promote the study to their family members and friends. The recruitment route of all participants will be recorded.

For the first 4 weeks of recruitment, the study will only be conducted in Beijing to allow all study processes to be piloted and altered as required, after which it will be implemented in the other three cities. Recruitment flow through the study is summarised in figure 2.

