### Ordering of assessments

Index tests will be conducted before the reference test for all participants, and the reference test will be administered by a different researcher who will be blind to the previous test results. To decrease the potential training effect within the index tests, the order of the peak flow and microspirometer will be alternated, that is, approximately half of the participants will perform peak flow first and vice versa. The screening questionnaires will always be completed after administration of salbutamol, during the 20 to 60 min time frame permitted prior to the reference test. Due to use of pre-printed study material, the order of the screening questionnaires will not be alternated.

Besides that, participants’ standing height (stadiometer) and weight (scales) will be measured. Participants will also be asked to complete a study questionnaire by themselves, in a separate area of the assessment clinic, and return the completed forms to the researcher. The study questionnaire (online supplemental appendix 2) will include items relating to the following topics: demographic data (sex, age, marital status, education level and deprivation); smoking status; exposures (biomass smoke, occupational exposure to chemicals and particulates); health (medical diagnoses (including COPD, asthma, TB and so on), comorbidities and respiratory symptoms); quality of life (COPD assessment test). A member of the research team will be available to help participants to complete questionnaires if necessary.

10.1136/bmjopen-2019-035738.supp2Supplementary data

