#### Analysis plan

Data will be analysed using Stata V.15.

Our primary analysis will compare the performance of a screening questionnaire (CAPTURE) with a handheld device (peak flow meter). Secondary analyses will include the comparative performance of each index test, as well as a comparison of strategies where we use a screening questionnaire and a handheld device.

The performance of each index test when diagnosing COPD (confirmed by quality diagnostic spirometry) will be investigated by presenting 2×2 tables and calculating the sensitivity, specificity, positive predictive value and negative predictive value, along with 95% CIs. For the tests with a continuous score, receiver operator curve analysis with area under the curve (with 95% CIs) will be produced. Comparisons of test accuracy between different index tests and different test strategies will be conducted using McNemar’s test and logistic regression modelling.

Sensitivity analyses will explore the impact on test performance of the index tests and strategies when using different definitions of COPD, including (i) a combination of spirometry data and clinical confirmation, and (ii) using the GOLD definition (fixed ratio (FEV_1_/FVC <0.7)) of airflow obstruction. Additional sensitivity analyses may explore the impact of spirometry quality as well as exploring optimal cut-points for the screening tests, in recognition that test performance will be dependent on the cut-points used.

A fully incremental cost-effectiveness analysis will be undertaken from a healthcare perspective to calculate the cost per true case detected for all pre-determined strategies. The strategies (including combinations) will be ordered by the number of true cases detected, from least to greatest, and the principles of dominance and extended dominance will be applied to eliminate redundant strategies from the analysis. Sensitivity analysis will be undertaken to explore the impact on results of any changes in assumptions, for example, time taken for a strategy.

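### The aim is undiagnosed COPD, but eligibility, accuracy tables and case counts take in people who already have a COPD diagnosis

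*Protocol article*

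**What the plan says.** All references are to the Protocol article.

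- **Aim:** to "identify the most effective and cost-effective screening strategy for identifying undiagnosed COPD among those aged 40 years or older in China". The Discussion opens with the same target.
- **Objectives:** "To determine the comparative test performance of all screening tests and strategies in diagnosing COPD (confirmed by quality diagnostic spirometry". The restriction to undiagnosed disease is absent here.
- **Inclusion criteria:** age 40 or over, and "Residing in the catchment areas of the participating CHSCs in the four cities".
- **Exclusion criteria:** these cover people who cannot carry out spirometry or have a contraindication to it, pregnancy or breastfeeding, and an earlier reaction to salbutamol. A prior COPD diagnosis is not listed.
- **Recruitment:** "Participants will be recruited to the study via two main routes, advertisement or doctor referral". Staff at the health centres hand the information sheet to visiting patients who may be eligible.
- **Ordering of assessments:** the study questionnaire covers "health (medical diagnoses (including COPD, asthma, TB and so on), comorbidities and respiratory symptoms", so a prior COPD diagnosis is on record for each participant.
- **Analysis plan:** "Our primary analysis will compare the performance of a screening questionnaire (CAPTURE) with a handheld device (peak flow meter". Further, "The performance of each index test when diagnosing COPD (confirmed by quality diagnostic spirometry) will be investigated by presenting 2×2 tables". The economic outcome is the cost for each true case detected. The stated sensitivity analyses vary the definition of COPD and, optionally, spirometry quality and cut-points. None uses prior diagnosis.

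**The concern.** A screening programme is judged by the patients it finds who were not known before. The aim says so, but the stated population and outcome do not follow it. Two results depend on the difference.

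First, yield and cost. A patient who already carries the diagnosis and is flagged by a strategy adds to its true cases, although screening has found nobody new. This needs no assumption about how the tests behave.

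Second, the primary comparison. The Introduction says that undiagnosed patients have fewer symptoms, and that questionnaire items include respiratory symptoms. A questionnaire may therefore perform better in known cases than in the cases the study is meant to find. If peak flow does not gain by the same amount, the difference in sensitivity among all cases is not the difference among undiagnosed cases.

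**Working it through.** **Inputs from the article.** Prevalence 12%; independent tests; sensitivities 95% vs 85% with N = 1622, and 90% vs 80% with N = 2279 (Sample size). About 2000 participants (Abstract). 96% of spirometry-confirmed cases undiagnosed, hence 4% known (Introduction).

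**Assumptions.** Two-sided alpha of 0.05, which the article does not state. Known shares of 10%, 20% and 30%, and all gaps in sensitivity between known and undiagnosed cases, are illustrative.

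**Step 1: reproduce the sample size.** With g = A/B and joint positivity A×B, the Alonzo formula for the number of cases is

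n = [(1.960 + 1.282)/ln g]² × (A + B − 2AB)/(AB).

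- 95 vs 85: ln g = 0.1112 and the variance term is 0.185/0.8075 = 0.2291, so n = 194.6 and N = 194.6/0.12 = 1621.6. The article states 1622.
- 90 vs 80: ln g = 0.1178 and the variance term is 0.26/0.72 = 0.3611, so n = 273.5 and N = 2279.2. The article states 2279.

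Both figures reproduce. A one-sided test would give 1322 and 1858, so two-sided 0.05 is the reading that fits. The sample size is not in error.

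**Step 2: cases already known.** Expected cases are 2000 × 0.12 = 240. At 4% known, 240 × 0.04 = 9.6, about 10. If a strategy flags known and undiagnosed cases equally often, the cost of each newly found case is the reported cost divided by (1 − share): 1/0.96 = 1.04 times the reported figure.

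**Step 3: primary comparison.** Shift in the sensitivity difference (questionnaire minus device) = known share × (questionnaire gap − device gap), where a gap is sensitivity in known cases minus sensitivity in undiagnosed cases.

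| Known share | Questionnaire gap 20, device 0 | Both 20 | Questionnaire gap 5, device 20 |
|---|---|---|---|
| 4% | +0.8 points | 0 | −0.6 |
| 10% | +2 | 0 | −1.5 |
| 20% | +4 | 0 | −3 |
| 30% | +6 | 0 | −4.5 |

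The design difference is 10 points.

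**Step 4: what restriction costs.** Power with 2000 enrolled = Φ(ln g × √(remaining cases/variance term) − 1.960), where remaining cases = 240 × (1 − share). The enrolment needed for 90% power is n/[0.12 × (1 − share)].

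| Known share | Known cases of 240 | Power, 95 vs 85 | Power, 90 vs 80 | Enrolment for 90% power (95 vs 85; 90 vs 80) |
|---|---|---|---|---|
| 0 | 0 | 94.9% | 85.9% | 1622; 2279 (as stated) |
| 4% | 9.6 | 94.1% | 84.5% | 1690; 2375 |
| 10% | 24 | 92.7% | 82.1% | 1802; 2533 |
| 20% | 48 | 89.6% | 77.5% | 2027; 2850 |
| 30% | 72 | 85.4% | 71.9% | 2317; 3257 |

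**The case against.** **The article is silent, not explicit.** It defines no analysis set, and a statistical analysis plan that is not shown could restrict it. A reader might infer that the investigators decided to keep known cases and to ignore the recorded diagnosis; no sentence says either. This part of the objection stands. It does not remove the point, because eligibility, objective and economic outcome are stated here, and together they describe a wider population than the aim does. An unseen restriction would depart from them.

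**The bias is not shown.** A reader might infer that known cases favour CAPTURE over peak flow. The documents do not support that as a fact. Fewer symptoms in undiagnosed patients bears on the questionnaire, but nothing is said about peak flow in known patients, whose lung function may be worse. If so, the shift could vanish or change sign, as Step 3 shows. Nor can one say that known patients score on items asking about an existing diagnosis. The questionnaires are in an appendix that is not shown, and the Introduction mentions only symptoms, exposures, smoking history and age. This objection stands in full.

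**The size is small.** The only documented share is 4%, and it gives less than one point against a design difference of 10. The shares of 10% to 30% have no source. Recruitment does not say that doctors will approach patients with known COPD, and the Discussion notes that voluntary screening finds much undiagnosed, asymptomatic disease. Against this, the 4% is a population figure, while health-centre attenders are one of the two recruitment streams, so it cannot be taken as the study's share.

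**The economic ranking may not change.** The analysis is incremental, and nothing here shows that any ordering or dominance result would alter. That is fair; the effect on the reported cost per case remains.

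**Conclusion.** The mismatch between the aim and the stated population and outcome is real. Followed as written, the plan counts known patients as cases found, which overstates yield and understates the cost of each newly found case. On the article's population figure this concerns about 4% of cases, 10 of 240. It would be more if recruitment enriches for known patients, by an amount the documents do not give.

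An effect on CAPTURE versus peak flow is possible, but its direction and size are undetermined. The 0.8 points at 4% known rests on an assumed 20-point gain for the questionnaire alone. A claim of established bias in the primary comparison would go beyond the documents. The case for the change is that the result should answer the stated aim, at little cost on the documented figure.

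**What to change.** Recruitment is reported as finished in December 2019, so the change belongs in the analysis. Define the primary set for test accuracy and for cost per case as participants with no self-reported COPD diagnosis on the study questionnaire. Report all participants as a sensitivity analysis, and give the number with a prior diagnosis by recruitment route, which is also recorded.

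This takes a sentence or two and no new data. The price is fewer cases: at 4% known and 2000 enrolled, power falls by about one point (94.9% to 94.1%, or 85.9% to 84.5%). The loss grows with the known share; at an assumed 30% it would be 85.4% or 71.9%. Count the remaining cases and restate the power before the primary comparison is run.

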#### Exclusion criteria

Unable to perform spirometry (eg, dementia or lack of teeth-cannot make a good seal).Contraindicated for spirometry (chest infection in the last 3 weeks, coughing up blood in the last month, severe angina, uncontrolled high blood pressure, pneumothorax or history in the last 3 months of tuberculosis, heart attack, detached retina or surgery on chest/abdomen/brain/ears/eyes).Currently pregnant/breastfeeding.Previous adverse reaction to salbutamol.

### Recruitment

Participants will be recruited to the study via two main routes, advertisement or doctor referral. Participating CHSCs and their satellite offices will advertise the study by displaying posters and sending messages to their secure/closed/other resident WeChat social media groups, inviting residents to contact the research team if they are interested in taking part. Potentially eligible patients visiting the participating CHSCs will be given a study information sheet by the healthcare professionals and invited to attend a study assessment with researchers. Study participants will also be encouraged to promote the study to their family members and friends. The recruitment route of all participants will be recorded.

For the first 4 weeks of recruitment, the study will only be conducted in Beijing to allow all study processes to be piloted and altered as required, after which it will be implemented in the other three cities. Recruitment flow through the study is summarised in figure 2.

